## Abstract

Chronic nonbacterial osteitis (CNO) is a rare auto-inflammatory bone disease affecting children and adults. Adult CNO is characterized by painful bone lesions, primarily of the anterior chest wall. There is no approved therapy for adult CNO. Current off-label treatments include intravenous bisphosphonates, which have been shown to alleviate pain through decreasing bone turnover. However, no adequately powered randomized controlled trials (RCTs) have been conducted. This double-blind, placebo-controlled RCT investigates the efficacy of intravenous pamidronate to decrease bone pain in adult CNO patients. Recruiting at the Dutch national referral center for CNO, adult patients with persistent bone pain despite non-steroidal anti-inflammatory drugs, or optionally other standard-of-care treatments are randomized to receive two courses of intravenous pamidronate (at 0 and 3 mo, 30 mg daily, on 3 consecutive d) or placebo. From 6 mo onwards, all patients receive open-label pamidronate for another two courses. The primary outcome is change in score for maximum pain from 0 to 6 mo. Secondary outcomes include change in quantitative intralesional bone turnover as measured on sodium-fluoride positron emission computed tomography ([^18^F]NaF-PET/CT), inflammation markers, shoulder function, general health, quality of life, fatigue, physical, and work activity. The pamidronate for pain in adult chronic nonbacterial osteitis trial addresses the need for evidence-based treatments in adult CNO. Results will directly impact daily clinical practice, either validating the use of intravenous pamidronate in CNO at the dose used in this trial or prompting the search for alternative regimens or agents. This trial was registered in EudraCT (reference 2020-001068-27) and the Dutch Trial Register (reference NL68020.058.20).

## Introduction

Chronic nonbacterial osteitis (CNO) is a rare autoinflammatory bone disease occurring in children and adults. In adults, the group involved in this trial, CNO primarily affects the axial skeleton, specifically the anterior chest wall. The spine, and to a lesser extent the mandible, and appendicular skeleton may also be involved.^1^^,^^2^ The precise pathophysiology of the disorder remains to be fully elucidated, although it has been shown to involve systemic cytokine dysregulation, leading to chronic bone inflammation and locally increased bone turnover.^3^ Over time, this results in erosions, degeneration, and excess bone formation in the form of hyperostosis and soft tissue calcification.^4^^,^^5^ Patients experience swelling and pain at the site of bone lesions, along with compromised functioning of adjacent joints. Therefore, CNO frequently causes decreased quality of life and work absence.^6^^,^^7^ While isolated bone involvement is most commonly observed, CNO patients may present with additional inflammatory features such as palmoplantar pustulosis, psoriasis, or arthritis.^2^

Clinical management of CNO is challenging, as there are neither evidence-based or standard therapies nor validated disease activity measures, resulting in significant variation in care world-wide.^8^ Current treatment options for both pediatric and adult CNO include non-steroidal anti-inflammatory drugs (NSAIDs) or cyclooxygenase 2 inhibitors (COXIBs), and in patients with persistent pain despite these agents, intravenous bisphosphonates or tumor necrosis factor alpha inhibitors (TNFi) may be administered.^2^^,^^8^^,^^9^ For pediatric CNO, consensus treatment plans centered around these agents have already been established,^9^ and for adult CNO, these are in development.^10^ However, randomized controlled trials (RCTs) are lacking for all treatments; their use in all age groups are primarily based on observational data from small cohorts and case series.

Bisphosphonates are antiresorptive agents that are selectively taken up by bone at sites of increased bone turnover. Here, they prompt function loss of osteoclasts, thereby exerting their anti-resorptive effect.^11^^,^^12^ The rationale for using bisphosphonates in both adult and pediatric CNO is based on the fact that nearly all patients with clinically active disease demonstrate increased bone turnover at affected sites, which in adults is mostly visualized through increased isotope uptake on nuclear imaging (see Figure 1).^2^ Increased bone turnover has been associated with pain in other metabolic bone diseases and is the driver of long-term structural tissue changes.^13^^,^^14^ It is thus hypothesized that bisphosphonates alleviate pain and prevent disease progression by decreasing local turnover in CNO as well.^15^ Besides, bisphosphonates may also target the inflammation that triggers the increase in bone turnover in CNO, by inhibiting the Farnesyl Pyrophosphate (FPP) synthase enzyme, which is essential for the survival not only of osteoclasts but also of FPP-dependent macrophages.^16^ Indeed, bisphosphonates, specifically pamidronate, have been shown to partially inhibit lymphocyte proliferation, monocyte/lymphocyte interaction, and gamma/delta T-cell numbers.^17^

**Figure 1 f1:**
[figure not shown]
Hypothesized working mechanism of pamidronate in chronic nonbacterial osteitis (CNO). Legend: IV: Intravenous, Ly: Lymphocyte, Neu: Neutrophil, Pla: Plasma cell.

The theoretical efficacy of bisphosphonates in CNO is supported by observational data, showing how bisphosphonates, mainly intravenous pamidronate, lead to a reduction in pain and radiologic signs of disease activity in adults and children.^18^^-^^28^ Similar positive results were found in a first small randomized, double-blind, placebo-controlled *pilot* trial comparing pamidronate to placebo in 12 adult CNO patients.^29^ Adequately powered trials are essential to infer a causal relationship regarding the efficacy of pamidronate to reduce pain in CNO, elucidate the underlying mechanisms, gain deeper understanding of the optimal treatment regimen, gather information on safety, and identify predictors of therapy response. Hence, we conceptualized and launched an investigator-initiated RCT PAMidronate for pain in adult Chronic Nonbacterial Osteitis (PAM-CNO). The design and conduct of this RCT presents challenges, due to the rarity of the disease, the absence of a clear disease definition, and limited understanding of relevant outcome measures. We therefore report its protocol, including the methodological obstacles characteristic of doing research in rare and poorly defined diseases such as CNO.

## Objectives

The primary objective of the PAM-CNO trial is to investigate the efficacy of intravenous pamidronate in reducing pain in adult CNO patients. Secondary objectives are to evaluate the effect of pamidronate on (1) a variety of patient-reported outcome measures (PROMs), (2) biochemical and immunological indices relevant to CNO, and (3) radiological parameters of disease activity and severity. Additional objectives are to evaluate baseline predictors of treatment response, to elucidate mechanisms by which pamidronate may reduce pain in CNO, and cost-effectiveness.

## Materials and methods

### Trial setting and design

This is a single-center, superiority trial conducted at the Centre for Bone Quality of the Leiden University Medical Center (LUMC), which is the Dutch national expertise and referral center for CNO. The trial starts with a 6-mo double-blind, randomized, placebo-controlled phase with 1:1 allocation of pamidronate or placebo (see Figure 2). Double-blind placebo-control was deemed necessary to prevent reporting bias because the trial’s primary outcome is patient-reported pain, which is susceptible to a placebo-effect. The 6-mo treatment duration is based on observational data from our center, where patients typically receive treatment for 6 mo or 1 yr (2 or 4 infusion cycles, administered in 3-mo intervals aligning with the physiological cycle of bone turnover). In consultation with representatives of the Dutch CNO patient association, it was agreed that 6 mo period of potential placebo treatment was acceptable if followed by the open-label extension. Therefore, the 6-mo randomized phase is followed by a 6-mo open-label phase.

**Figure 2 f2:**
[figure not shown]
Study structure of the PAM-CNO trial.

### Eligibility criteria

Patients ≥18 yr of age with an established diagnosis of CNO are the population base of this study. In the absence of validated classification criteria for CNO, the primary diagnostic criterion is sterile bone inflammation at one or more skeletal sites in the anterior chest wall, with or without involvement of other skeletal sites. This is identified based on clinical features (inflammatory bone pain and possibly signs of inflammation on physical exam), biochemical markers (mild to moderate increase in inflammation markers, though often these are within normal range), and imaging findings (bone marrow edema, sclerosis, hyperostosis, erosions, ligament ossification, ankylosis of joints, and increased isotope uptake on nuclear imaging). If a bone biopsy is performed, histopathology compatible with sterile bone inflammation includes nonspecific inflammation and increased bone turnover. Sterile bone inflammation, and herewith diagnosis of CNO, is confirmed through a multidisciplinary, integrated assessment. Of note, this definition of sterile bone inflammation/CNO means that patients can have varying skeletal distribution patterns and may or may not have additional (extra)skeletal features such as arthritis, enthesitis, sacroiliitis, palmoplantar pustulosis, psoriasis, or severe acne.

Further inclusion criteria are as follows:

Score for maximal pain (concerning bone pain at lesion sites over the past week) ≥6/10 as measured by Brief Pain Inventory (BPI).^30^Insufficient response to at least one NSAID/COXIB at maximum approved and tolerated dosage, intolerance or contraindication to these agents, or indication for direct second-line treatment due to active vertebral lesions.A washout period of prior bisphosphonates (6 mo since last administration).

Exclusion criteria are as follows:

<18 yr of age.Active pregnancy wish, active pregnancy, or nursing.Generalized pain without pain at the site of CNO lesions.Bisphosphonate allergy.Estimated glomerular filtration rate < 30 ml/min.Uncontrolled endocrine comorbidities, active cancer (treatment), or other severe comorbidity preventing the attendance of study visits.Severe language barrier preventing the completion of questionnaires.Mental disability.

Of note, eligible patients receive supplementation before study inclusion if serum 25-hydroxy vitamin D is <50 nmol/L. Eligible patients with poor dental hygiene are included only after consultation and approval from an oromaxillary surgeon, due to the small risk of osteonecrosis of the jaw (ONJ) associated with bisphosphonate treatment.^31^

### Interventions

Pamidronate is administered at 0 and 3 mo, an interval that is common practice due to the known pharmacodynamic and pharmacokinetic properties of this agent and which aligns with the physiological cycle of bone turnover.^12^ In total, 90 mg is administered over the course of 3 d of 30 mg each. The splitting of the total dose is done to get optimal uptake at sites of increased bone turnover, as pamidronate is quickly cleared from the circulation.^12^ The 30-mg dose is diluted in 250 ml 0.9% saline, administered intravenously in 2 h. Placebo is administered as 250 ml of saline 0.9% at the same speed, also over 3 consecutive d. Randomization, preparation, and (blind) labeling of pamidronate and placebo are done by the certified LUMC pharmacy according to the Good Manufacturing Practice-guidelines.

### Concomitant care and deviations from allocated interventions

For concomitant care, both the placebo and intervention arms allow additional NSAIDs/COXIBs at stable dosages. Intake of NSAIDs/COXIBs is monitored by the research team through a diary completed by the patient at 2 fixed d per wk (Wednesday and Saturday). NSAIDs/COXIBs may be decreased or discontinued at any point if pain levels allow. Principally, NSAIDs/COXIBs are not increased, except in cases of unacceptable persistent pain, where they are considered escape medication.

Since CNO patients may suffer from other (extra)skeletal manifestations, it is anticipated that some patients may be taking other standard-of-care anti-inflammatory treatments, such as methotrexate for arthritis or biologic disease-modifying anti-rheumatic drugs (biologic DMARDs) for psoriasis. To limit undertreatment of such patients, all standard-of-care treatments may be continued throughout the trial provided they are taken at stable dosage. Importantly, the main inclusion criterion of a ≥6/10 score for maximal bone pain must be met despite use of these standard-of-care treatments, as evidence for insufficient control of osteitis. Also, if standard-of-care treatments have been discontinued or changed shortly before anticipated inclusion, a washout period is installed as recommended based on half-life by the pharmacology department (eg, 1-4.5 mo for TNFi, depending on the agent and administration route). During the trial, standard-of-care anti-inflammatory treatments are not newly started or increased unless urgently needed. Patients are permitted to continue, start, or discontinue physical therapy as needed.

### Outcomes and statistical analyses

The primary outcome of this trial is score of maximal pain on BPI (numerical rating scale 0-10) measured at the end of the 6-mo randomized phase. We will compare the difference between groups by generalized linear mixed model (GLMM) with analysis of covariance (ANCOVA) to account for baseline scores. The primary analysis will be intention-to-treat (see Table 1 and Figure 2). Secondary outcomes include a range of patient-reported,^32^^-^^40^ biochemical, and radiological outcomes, as well as their intercorrelation, baseline factors associated with treatment response,^41^^,^^42^ and cost-effectiveness^43^ (see Table 1 for measurement instruments, statistical analyses, and timepoints). Sensitivity analyses include a per-protocol and an as-treated analysis of the primary outcome. Missing data on the outcomes not evaluated by GLMM are imputed and handled through maximum likelihood techniques. No interim analyses are conducted.

**Table 1 TB1:** Primary and secondary outcomes of the PAM-CNO trial.

	**Outcome**	**Instrument**	**Timepoint of collection**	**Statistical analysis**	**Timepoint of analysis**
**Primary**	Score for maximal pain at CNO lesion sites	BPI	0, 3, 6, 9 and 12 mo	GLMM with ANCOVA	6 mo
**Secondary**	Score for minimal, average, and activity-related pain at CNO lesion sites	BPI	0, 3, 6, 9 and 12 mo	GLMM with ANCOVA	6 and 12 mo
**PROMs**	Shoulder function	SFA			
		SRQ			
	General health	SF-36			
	Quality of Life	EQ-5D			
	Work activity	Work Activity Score			
	Physical activity	IPAQ			
	Fatigue	MVI-20			
	Patient global	PGIC			
	Burden of a relative	Carer-QoL			
	Pain diary	NRS 0-10 for pain	2 d per wk, for entire 1-yr trial span	GLMM	6 and 12 mo
	Achievement of mild pain, as defined by ≤4/10 for maximal pain on BPI	BPI	0, 3, 6, 9, and 12 mo	Chi-square between groups, reported as odds ratio with 95% confidence interval	3, 6, and 12 mo
	Achievement of ≥50% reduction in maximal pain on BPI	BPI	0, 3, 6, 9, and 12 mo		
	% of patients with reduction in standard dose of NSAIDs/COXIBs	-	3, 6, and 12 mo		
**Biochemical**	ESR, CRP	Standard laboratory evaluation	0, 3, 6, 9, and 12 mo	GLMM with ANCOVA	6 and 12 mo
	Pro- and anti-inflammatory cytokines	ELISA			
	Bone markers	ELISA			
	mRNA expression	MLPA	0, 6, and 12 mo		
	T-lymphocyte counts	FACS			
**Radiological**	Progression or regression of either sclerosis, hyperostosis, erosions, ankylosis, or soft tissue calcification	[^18^F]NaF-PET/CT	0, 6, and 12 mo	Chi-square between groups, reported as odds ratio with 95% confidence interval	6 and 12 mo
	Quantitative isotope uptake in CNO-lesions by SUV_max_			GLMM with ANCOVA	6 and 12 mo
**Correlations**	SUV_max_ with maximal and average pain	[^18^F]NaF-PET/CT and BPI	0, 6, and 12 mo	Pearson’s R or Spearman’s Rho as appropriate	0, 6, and 12 mo
	SUV_max_ with ESR and CRP	[^18^F]NaF-PET/CT and standard laboratory evaluation	0, 6, and 12 mo		
**Predictors of treatment response**	Diagnostic delay (yr)	-	0 mo	GLMM in pamidronate group, with maximal pain score on BPI as outcome	6 mo
	Baseline lesional isotope uptake (SUV_max_)	[^18^F]NaF-PET/CT	0 mo		
	Degree of central sensitization	CSI	0, 6, and 12 mo		
	Degree of neuropathic pain	PAIN-DETECT	0, 6, and 12 mo		
	Baseline presence of erosions, hyperostosis, and/or ankylosis	[^18^F]NaF-PET/CT	0 mo		
	Baseline presence of elevated ESR and/or CRP	-	0 mo		
**Cost-effectiveness**	Trial-based cost-utility from a societal perspective in accordance with the Dutch health-economics guidelines	IPCQ	0, 3, 6, 9, and 12 mo	Trial-based cost-utility analysis with costs-per-quality adjusted life yr, based on net-benefit analysis and friction-cost method.	6 and 12 mo (extrapolated to life-long discounted time horizon)

Abbreviations: ANCOVA; Analysis of Covariance, [18F]NaF-PET/CT; Sodium-fluoride positron emission tomography, BPI; Brief Pain Inventory, CarerQoL; Care-related Quality of Life Instrument, CNO; Chronic Nonbacterial Osteitis, COXIBs; Cyclooxygenase 2 Inhibitors, CSI; Central Sensitization Inventory, FACS; Fluorescence Activated Cell Sorting, ELISA; enzyme-linked immunosorbent assay, EQ-5D; EuroQol 5-Dimension, ESR; Erythrocyte Sedimentation Rate; GLMM; Generalized Linear Mixed Model, IPAQ; International Physical Activity Questionnaire, MLPA; Multiplex Ligation-dependent Probe Amplification, MVI-20; Multidimensional Fatigue Inventory-20, NRS; Numerical Rating Scale, NSAIDs; Non-Steroidal Anti-Inflammatory Drugs, PGIC; Patient Global Impression of Change, SF-36; Short Form Health Survey, SRQ; Shoulder Rating Questionnaire, SUV_max_; Standardized Maximum Uptake Value.

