### Sample size

Based on our observational data on adult CNO patients with a maximum pain score of ≥6/10 treated with intravenous pamidronate, BPI score for maximal pain is expected to decrease from a mean of 8 with standard deviation (±) of 2 to a mean of 6 ± 2 in the active treatment arm. In rheumatoid arthritis, the placebo effect on pain has been estimated at 16-22 at a 100-mm scale.^44^ However, because evidence-based treatments for CNO are entirely lacking—potentially reducing patient confidence in any given treatment—and many patients present with advanced disease due to diagnostic delays, we anticipate a smaller effect in the placebo arm of this trial, with pain levels decreasing from 8 ± 2 to 7.5 ± 2. We use a power of 80% and an alpha of 0.05. As the primary analysis is done with ANCOVA, adjustment for correlation between baseline and follow-up scores was done (Pearson’s correlation coefficient calculated at 0.479), with a required sample size of 35 patients per arm (total *n* = 70).^45^ In case of screen failure or drop-out before the 6-mo primary endpoint, patients will be replaced to meet the required sample of 70.

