### Trial workplan and data collection

Visits are scheduled at 0, 3, 6, 9, and 12 mo (see Figure 2), with pamidronate or placebo administered at 0 and 3 mo, and open-label pamidronate administered at 6 and 9 mo. Visit 12 is an outpatient consultation without infusions.

At every visit, patients complete a set of questionnaires (see Table 1). BPI and shoulder function assessment (SFA) are filled out in writing on paper as part of standard care [recorded in the electronic health record and case report form (CRF)]. All other questionnaires are digitally completed by the patient in the CRF. A relative, if included, digitally completes the questionnaire on carer burden at every timepoint as well. Patients are requested to keep a digital pain and fatigue diary (NRS 0-10, range from pain/fatigue to 10 for worst pain/fatigue) and record their analgesic use for 2 fixed d each wk (Wednesday and Saturday) throughout the entire trial.

Other CRF-entries include the recording of medication changes, adverse events, physical examination, and fasting-state laboratory investigations (complete blood and differential count, CRP, ESR, kidney function, calcium/albumin, phosphate, alkaline phosphatase, gammaGT, bone turnover markers C-terminal telopeptide of type I collagen and Procollagen type I N-terminal propeptide, parathyroid hormone, 25-hydroxy vitamin D).

Serum and plasm are stored within 2 h after specimen withdrawal at −80 °C, for future batch analysis of inflammatory markers and additional bone markers with enzyme-linked immunosorbent assay. At 0, 6, and 12 mo, additional specimens are collected for isolation of mRNA and peripheral blood mononuclear cells (harvested <2 h after blood withdrawal and stored in liquid nitrogen). In batch, Multiplex Ligation-dependent Probe Amplification-assay characterizing mRNA expression will be performed, after which specific T-cell subsets of interest will be counted with Fluorescence Activated Cell Sorting, including Th-17 and γδ T-cells.

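### Table 1 plans the pain-diary comparison without the baseline adjustment given to the other between-group GLMMs; adding a 0-month BPI score would be a near-free, minor gain

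*Protocol article*

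**What the plan says.** The protocol article, Outcomes and statistical analyses, describes the primary analysis thus: "We will compare the difference between groups by generalized linear mixed model (GLMM) with analysis of covariance (ANCOVA) to account for baseline scores". Table 1 repeats "GLMM with ANCOVA" for the primary BPI score, the other BPI pain scores, the biochemical outcomes and SUVmax. The questionnaire rows below the BPI row have blank cells and appear to inherit the same method.

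The pain diary (a 0-10 numerical rating of pain) has its own entries: collection "2 d per wk, for entire 1-yr trial span", method GLMM, analysis at 6 and 12 months. The only other plain GLMM in the table is for predictors of response. That model is fitted within the pamidronate group and compares no arms.

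Trial workplan and data collection confirms that the diary is kept "for 2 fixed d each wk (Wednesday and Saturday) throughout the entire trial" and mentions no run-in before the first infusion. On the BPI, the same section says: "At every visit, patients complete a set of questionnaires". Visits start at 0 months, and a BPI maximal pain score of at least 6 is an inclusion criterion, so every randomised patient has a baseline pain score. The Blinding section gives 1:1 randomisation in blocks of 2, 4 and 6 and mentions no stratification by pain.

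**The concern.** The article has a rule for between-group mixed models, which is to adjust for baseline, and the diary row departs from it without a stated reason. The absence of a pre-infusion diary score may explain the different label, but it does not prevent adjustment. A covariate need only be prognostic and measured before treatment. It need not come from the same instrument.

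The mixed model does not supply the adjustment by itself. Treatment varies between patients. A random intercept describes how entries within a patient correlate, but the between-patient variation that baseline pain could explain stays in the error of the treatment contrast. More diary entries per patient do not remove it.

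At stake are the precision of the diary contrast and its exposure to whatever difference in baseline pain arises by chance between two arms of 35.

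**Working it through.** **Inputs.** From Sample size: 35 per arm, SD 2, expected 6-month difference 7.5 − 6 = 1.5, and for BPI maximal pain a "correlation coefficient calculated at 0.479". Also from there: "We use a power of 80% and an alpha of 0.05", taken here as two-sided. The article gives no SD for the diary and no diary-BPI correlation. Both are borrowed from the BPI as assumptions, and the correlation is varied.

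**The plan's own figure.** There is none for the diary. For the primary ANCOVA, n per arm = 2 × [2 × √(1 − 0.479²) × (1.960 + 0.842) / 1.5]² = 21.5, so 22, against the stated 35. That mismatch is a separate matter. Here 35 is used only as the number analysed.

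**Precision.** The ratio of unadjusted to adjusted variance is 1/(1 − r²).

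- r = 0.3: 1/0.910 = 1.10, so 10% more variance and a standard error 5% larger.
- r = 0.479: 1/0.7706 = 1.30, so 30% more variance and a standard error 14% larger (√1.298 = 1.139).
- r = 0.6: 1/0.640 = 1.56, so 56% more variance and a standard error 25% larger.

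At r = 0.479 and SD 2:

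- Unadjusted SE = 2 × √(2/35) = 0.478, 95% half-width 0.94.
- Adjusted SE = 0.478 × √0.7706 = 0.420, 95% half-width 0.82.
- Information: 70/0.7706 = 90.8, so 70 adjusted patients are worth about 91 unadjusted.
- Power for a 1.5-point difference: 88.1% unadjusted, 94.7% adjusted.
- Power for a 1.0-point difference: 55.2% unadjusted, 66.4% adjusted.

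These are large-sample figures. Estimating the covariate slope costs a factor of about 1 + 1/(70 − 4) = 1.015, which turns 1.30 into 1.28.

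**Chance imbalance.** The between-arm difference in mean baseline pain has standard error SD_baseline × √(2/35), which is 0.48 points at SD 2. Given an imbalance, the unadjusted contrast shifts by the slope r × SD_diary/SD_baseline times that imbalance. For a one-SE imbalance this is r × SD_diary × √(2/35) = 0.479 × 0.478 = 0.23 points, and for a 1.96-SE imbalance it is 0.45 points.

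The baseline SD cancels. If it were 1.4 (illustrative, since entry requires a score of at least 6), the one-SE imbalance would be 0.33 points, but the slope would rise to 0.479 × 2/1.4 = 0.684 and the shift would still be 0.23. The shift falls to 0.16 only if the diary SD is also 1.4.

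**The case against.** The strongest reply is that one table cell names a model family and need not list every term. The full protocol exists but is not shown, and it or an analysis plan may already include the covariate. The label also has an innocent explanation: the ANCOVA rows adjust for the outcome's own 0-month score, and the diary has none described. A repeated-measures GLMM without baseline is an accepted analysis.

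Part of this stands. The article does not say that covariates are barred from the diary model, and the unadjusted analysis is valid. But the cell is not merely silent. It stands in contrast to rows that carry the ANCOVA label, and the text says what that label means. The predictor row is no counterexample, because it compares no arms.

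A second reply is that the diary and the BPI may not measure the same thing. The BPI item used at entry concerns maximal bone pain at lesion sites over the past week, while the diary is described only as a pain rating. This stands as a caution about the size of r and about which BPI item to choose. It does not undo the point, because any useful correlation brings a gain.

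A reader might also infer that the diary result would be biased or its type I error inflated. Randomisation rules out both. Nor does the article make the diary the main support for the primary endpoint. It is one of many secondary outcomes, the other BPI pain scores are already adjusted, and the named sensitivity analyses of the primary outcome are per-protocol and as-treated.

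**Conclusion.** The point holds as a minor one. The diary row states a method that differs from the other between-group GLMM comparisons, and a suitable covariate is already collected. The cost of leaving it out is lost precision plus a conditional shift when baseline pain happens to differ between the arms.

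The size depends on a diary-BPI correlation that the article does not give. On the borrowed value of 0.479, the unadjusted standard error is 14% larger. Over correlations of 0.3 to 0.6 it is 5% to 25% larger. The 14% should therefore not be read as a known loss. The 0.23-point shift for a one-SE imbalance further assumes a diary SD of 2.

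The consequence is mainly for the 6-month comparison. By 12 months both arms have received open-label pamidronate, so the between-arm contrast there carries less weight.

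**What to change.** Before unblinding, change the diary row of Table 1 to "GLMM with ANCOVA" and name one 0-month BPI item as a fixed covariate in the 6- and 12-month diary models. Maximal pain would match the primary analysis and is available for every patient through the entry criterion. Average pain is the alternative if it fits the diary wording better. The choice should be written down now, so that no selection between adjusted and unadjusted diary results, or between BPI items, can follow the data. If the full protocol or analysis plan already specifies such a covariate, the article's table only needs to be aligned with it.

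The cost is one label and one model term, with no new data and no extra patient burden. It is still feasible on the article's own account: 61 of 70 patients had been included, analysts are blinded, and no interim analysis is planned.

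### The ≤4/10 maximal-pain outcome is compared by an unadjusted chi-square although baseline pain is collected and prognostic: the test is valid, but some precision is lost and any realised baseline imbalance carries into the odds ratio

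*Protocol article*

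**What the plan says.** In the protocol article, Outcomes and statistical analyses, Table 1 lists "Achievement of mild pain, as defined by ≤4/10 for maximal pain on BPI" as a secondary outcome, analysed at 3, 6 and 12 months. The method given is "Chi-square between groups, reported as odds ratio with 95% confidence interval"; no covariate is named.

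The primary outcome in the same section is the same maximal BPI score kept as a number. It is compared by "generalized linear mixed model (GLMM) with analysis of covariance (ANCOVA) to account for baseline scores". BPI is collected at 0 months.

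Eligibility criteria require "Score for maximal pain (concerning bone pain at lesion sites over the past week) ≥6/10 as measured by Brief Pain Inventory (BPI"), so on a 0-10 scale every patient starts between 6 and 10 and none is a responder at entry. The Blinding section describes 1:1 randomisation in blocks of 2, 4 and 6, and mentions no stratification by pain.

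The Sample size section expects maximal pain on pamidronate to go "from a mean of 8 with standard deviation (±) of 2 to a mean of 6 ± 2", and on placebo expects "with pain levels decreasing from 8 ± 2 to 7.5 ± 2". It gives a baseline to follow-up "correlation coefficient calculated at 0.479".

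**The concern.** The cut-off is a fixed level, so how hard it is to reach depends on where the patient starts. Someone entering at 6 needs a fall of 2 points; someone entering at 10 needs a fall of 6. The plan treats baseline pain as worth adjusting for when the score is analysed as a number, then leaves it out when the same score is cut at 4.

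Two things follow. Prognostic information held for every patient goes unused. And with 35 patients per arm and no stratification by pain, a chance difference in starting pain shifts the responder odds ratio, with no planned adjusted analysis to show by how much. Clinicians quote responder percentages readily, and an odds ratio that seemed to disagree with the baseline-adjusted primary result would be hard to explain afterwards.

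**Working it through.** **Inputs.** From Sample size: follow-up means 6 and 7.5, SD 2, mean baseline 8 with SD 2, r = 0.479, 35 per arm. From Eligibility criteria: baseline range 6 to 10. Assumed: two-sided 5% alpha, normal latent scores rounded to whole numbers (so ≤4 means a latent score below 4.5), and the shape of the baseline distribution. With a mean of 8 on a 6-10 range, an SD of 2 is possible only if every patient scores 6 or 10. Results are therefore given for baseline SDs from about 1.4 (uniform on 6 to 10) to 2.

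**The plan's own figure.** The article gives no response rate or power for this outcome, so there is nothing to reproduce for it. The 35 per arm is used here as the planned size. It does not follow from the stated ANCOVA inputs (2 × [2 × (1.960 + 0.842)/1.5]² = 27.9; 27.9 × (1 − 0.479²) = 21.5, so 22 per arm), but that is a separate matter.

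**1. Implied response rates at 6 months.** Pamidronate: Φ((4.5 − 6)/2) = 22.7%. Placebo: Φ((4.5 − 7.5)/2) = 6.7%. The odds ratio is 4.1. With an exact cut at 4 the rates are 15.9% and 4.0%, and the odds ratio is 4.5.

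**2. How far baseline predicts response.** The share of follow-up variance explained is 0.479² = 0.23. The chance of ≤4 at baseline b is Φ((4.5 − [mean + slope × (b − 8)])/(2√(1 − 0.479²))), with slope = 0.479 × 2/baseline SD.

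| Baseline SD | Arm | b = 6 | b = 10 |
|---|---|---|---|
| 2 (as stated) | pamidronate | 38% | 8% |
| 2 (as stated) | placebo | 12% | 1% |
| 1.41 (assumed) | pamidronate | 47% | 5% |
| 1.41 (assumed) | placebo | 17% | 0.7% |

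Baseline is clearly prognostic under either SD. The correlation between baseline score and response is about −0.29.

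**3. Power, 35 per arm, simulated (8,000 trials per setting).** Chi-square about 50%; baseline-adjusted logistic score test about 53%. Across four assumed baseline distributions the gain is 2 to 4 points. At r = 0.3 it is about 1 point and at r = 0.7 about 10. A separate simulation of penalised likelihood gave 51% adjusted, against 47% unadjusted penalised and 49% chi-square. In sample-size terms, going from 50% to 53% power is worth ((1.960 + 0.075)/1.960)² = 1.08, or about 8%.

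**4. Type I error.** With no drug effect the chi-square rejects 4.7 to 4.9% of the time. If both arms respond at the placebo rate there are about 70 × 0.067 = 4.7 responders in total. The ordinary adjusted likelihood-ratio test then rejects about 7.6 to 8.3% of the time. Penalised likelihood stays between 2.5% and 5%.

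**5. Effect of a realised imbalance.** The SD of the difference in mean baseline pain is SD × √(2/35): 0.33 points for SD 1.4 and 0.48 for SD 2. The simulated slopes of the log odds ratio are −0.61 and −0.41 per point of imbalance. With the simulated imbalance SDs of 0.34 and 0.48, a one-SD imbalance gives factors of exp(−0.61 × 0.34) = 0.81 and exp(−0.41 × 0.48) = 0.82, or about 1.2 in the other direction. At 1.96 SD the factor is 1.23^1.96 = 1.5, so an expected odds ratio of 4.1 would become about 2.7 or just over 6.

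**The case against.** The best case for leaving the plan alone is that nothing in it is wrong. A chi-square on a binary outcome in a 1:1 randomised trial is valid, the odds ratio is a legitimate marginal comparison, and the confidence interval already allows for chance imbalance. That interval is wide. At 23% against 7% with 35 per arm, the SE of the log odds ratio is √(1/8.05 + 1/26.95 + 1/2.45 + 1/32.55) = 0.775, so an odds ratio of about 4.0 has a 95% interval of about 0.9 to 18. Against that, a factor of 1.5 at the extreme is small. The same score is also analysed with baseline adjustment as the primary outcome, and no main conclusion rests on this row.

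All of that stands, and it keeps the point modest. It does not remove it. Valid on average over randomisations is not the same as well estimated in the one trial that is run, and the precision given up comes from a covariate already in the database.

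A reader might infer more than the article supports:

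- That baseline pain largely decides who reaches 4. With r = 0.479 it explains about 23% of follow-up variance, and even at baseline 6 more than half of pamidronate patients would miss the cut-off.
- That adjustment would cure the low power. It would not: power stays near 50%, because few patients respond and there are only 35 per arm.
- That an odds ratio moved from 4.1 to 2.7 is to be expected. That is the 95% limit of imbalance, not a typical trial.

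**Conclusion.** The point holds as a worthwhile improvement to one secondary outcome, not as an error that invalidates a result. Leaving out a collected, prognostic baseline costs about 2 to 4 points of power at roughly 50%, and lets a realised imbalance move the odds ratio by a factor of about 1.2 (one SD) to 1.5 (95% extreme).

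These sizes rest on the article's means, follow-up SD and correlation, on normal latent scores, and on an assumed baseline SD of 1.4 to 2. They apply at 6 months, because the article gives no expected values at 3 months. The ≥50%-reduction outcome is not affected in any way that matters, since its cut-off already scales with the starting score.

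**What to change.** Before unblinding, specify for the ≤4/10 outcome at 3 and 6 months a logistic regression on arm and 0-month maximal BPI pain, fitted by penalised (Firth) likelihood. Fix the penalised method in advance: responders may be few, and the ordinary likelihood-ratio test is then anticonservative.

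Report standardised responder percentages per arm and their difference with a 95% confidence interval, because the adjusted odds ratio is a conditional measure and is not comparable with the unadjusted one. Firth estimation pulls predicted probabilities towards one half when events are sparse, so state that the intercept is re-estimated to match the observed overall responder proportion before standardising.

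Keep the chi-square and its odds ratio as supplementary, and leave the ≥50%-reduction row as it is.

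The cost is a few lines in the analysis plan and minor extra analysis work. No new data, visits or patients are needed. If allocation has already been revealed to the analysts, the adjusted analysis should be labelled post hoc.
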